## Abstract

**Background:**

Model projects for flexible and integrated treatment (FIT) in Germany aim at advancing the quality of care for people with mental disorders. A new FIT model project was established in 2017 at the Department of child and adolescent psychiatry (KJP) of the University Hospital Tübingen (Universitätsklinikum Tübingen, UKT). The study design of EVA_TIBAS presented here describes the evaluation of the FIT model project at the KJP of the UKT. This evaluation aims at quantifying the anticipated FIT model project changes, which are to improve patients’ cross-sectoral care at the same maximum cost as standard care.

**Methods:**

EVA_TIBAS is a controlled cohort study using a mix of quantitative and qualitative methods. The FIT evaluation consists of three modules. In Module A, anonymized claims data of a statutory health insurance fund will be used to compare outcomes (duration of inpatient and day care psychiatric treatment, inpatient and day care psychiatric length of stay, outpatient psychiatric treatment in hospital, inpatient hospital readmission, emergency admission rate, direct medical costs) of patients treated in the model hospital with patients treated in structurally comparable control hospitals (estimated sample size = ca. 600 patients). In Module B, patient-reported outcomes (health related quality of life, symptom burden, return to psychosocial relationships (e.g. school, friends, hobbies), treatment satisfaction, societal costs) will be assessed quantitatively using validated questionnaires for the model and two control hospitals (estimated sample size = ca. 300 patients). A subsequent health economic evaluation will be based on cost-effectiveness analyses from both the insurance fund’s and the societal perspective. In Module C, about 30 semi-structured interviews will examine the quality of offer, effects and benefits of the service offered by the social service of the AOK Baden-Württemberg (for stabilizing the overall situation of care in the family) in the model hospital. A focus group discussion will address the quality of cooperation between employees of the university hospital and the social services.

**Discussion:**

The results of this evaluation will be used to inform policy makers whether this FIT model project or aspects of it should be implemented into standard care.

**Trial registration:**

This study was registered at ClinicalTrials.gov PRS (ID: NCT04727359, date: 27 January 2021).

## Background

According to the German KiGGS-Survey [1], about 20% of all children and adolescents in Germany are affected by mental and behavioral problems [2]. While about 6% of those under the age of 18 years are mentally ill according to diagnostic criteria and, as a consequence, are in need of treatment, about 50% of those in need do not receive treatment [3, 4]. Reasons for this poor claim of medical services among young patients might be low or delayed help-seeking behavior due to stigma, insufficient knowledge about access to mental health care services and lack of treatment capacities [5, 6]. Moreover, most adult mental health disorders have their onset in adolescence [7, 8]. These circumstances put further emphasis on the need of early prevention and adequate treatment of the young.

The treatment of patients with mental disorders in Germany is mainly provided by outpatient care, e.g. medical specialists, child and adolescent psychotherapists or psychiatric outpatient departments in hospitals (Psychiatrische Institutsambulanz (PIA)), the latter being for patients in need of particularly intensive and complex near-hospital care due to the nature, severity or duration of their mental disorder [3]. Mental health services are also provided in the inpatient sector, e.g. by hospitals with a Department of child and adolescent psychiatry (KJP). In addition, social service providers, such as the child and youth welfare service or educational and family counselling centers as well as the schools, e.g. school psychology services or schools for educational aid, support child and adolescent mental care [3]. Many other services, e.g. assisted living, social assistance or vocational reintegration, are also strongly involved in the care of patients with mental disorders.

The number of children treated in hospitals and diagnosed with a mental disorder has increased in Germany over the last years (2007–2014: + 38%) [3, 5], while the average duration of stay has decreased (2007–2014: − 14%) and at the same time, emergency rates have increased (2011: 29% vs. 2013: 38%) [3, 9, 10]. This situation is partly driven by a fraction of young patients being hospitalized with a high severity and complexity of psychosocial problems [9].

KJPs in Germany usually treat young patients under the age of 18 years. This means that treatment of patients in a KJP reaching the age of 18 years needs to be transferred to adult psychiatry. Thus, the entry into adulthood is a fragile period for those patients. Considering the care of young patients with mental disorders, further non-medical social service providers, such as schools, day care centers, youth welfare offices and the family system itself, need to cooperate closely with the health care providers. An interdisciplinary approach to care thus constitutes the core of the treatment in KJPs, including its implementation into the environment of the young patient, involving the custodians of the child or adolescent, who, in most cases, are the parents, [3].

The financing and operation of the German health care system is separated into sectors, each of which involves different legal grounds and stakeholders. For example, the remuneration of inpatient treatment differs from the one of outpatient treatment in the hospital and again from the remuneration of resident physicians, leading to a fragmented system with sometimes opposing interests of stakeholders [11]. The social and educational sectors are again organized and financed by different parties. Altogether, this strict separation of sectors in terms of regulatory frameworks, financing and remuneration hampers a patient-oriented management of psychiatric care. Treatment continuity is, however, particularly important for patients with mental disorders. The current strict separation of the financing hinders needs-adapted treatment forms as alternative treatment, such as intensive day care treatment or individual home care treatment, and are often not financially covered leading to more-than-necessary inpatient treatment. There is an ongoing debate in Germany on how to solve the problem of fragmentation at the federal level [12]. Several initiatives aim to reduce the fragmentation in the German health care system, e.g. projects for integrated or cross-sectoral care based on § 64b or 140a of the German Social Code, Book V (SGB V) [13, 14].

The introduction of § 64b SGB V in 2012 created the possibility of setting up FIT model projects for the advancement of the quality of care for people with mental disorders. The objective is to improve patient-oriented cross-sectoral care or optimize patient care. For this purpose, statutory health insurance (SHI) funds can close contracts with hospitals and jointly establish new and exclusive care and financing structures, forming the core of FIT model projects. The aim of the legislature was to establish these models, including KJP, in all 16 German federal states. By 2021, these goals have not yet been achieved. FIT models have only been established in 12 of the 16 federal states so far and only 7 of 22 FIT models have addressed children and adolescents. All FIT model projects must be scientifically and independently evaluated according to a supplementary law (§ 65 SGB V) [15].

Two German SHI funds (AOK Baden-Württemberg and the SVLFG, an agricultural health insurance fund)), have, together with the UKT, developed a FIT model project in the hospital’s Department of child and adolescent psychiatry, which will be tested for a total of 8 years starting from October 2017. This FIT model project is the only FIT model so far that exclusively targets children and adolescent at a KJP. Roughly 50% of patients treated in the KJP are insured through one of the two contracting SHI funds. The core of the model constitutes the Therapeutic Intensive Treatment in the Outpatient Setting (TIBAS, acronym for the German phrase “**T**herapeutische **I**ntensiv**b**ehandlung im **A**mbulanten **S**etting”), an approach that aims to provide more cross-sectoral services through flexible treatment intensities compared to standard care.

TIBAS as an intensive form of outpatient treatment intends to enable earlier discharge from the inpatient setting to improve psychosocial functioning by allowing patients to return into their social environment in a more timely manner. Different TIBAS levels have been implemented, representing different treatment intensities and frequencies, which can be deployed flexibly according to patients’ needs. A person-centered case manager accompanies patients throughout the whole treatment period. If necessary, patients and especially family members are accompanied by the social service of the AOK Baden-Württemberg and supported with regard to stabilizing the overall situation of care (psychosocial counseling and networking with other care providers, etc.). The social service supports custodians or relatives in unstable care situations. It follows a systemic approach that is based on the assumption that a sustainable stabilization of the child or adolescent can only be achieved through the stabilization of the custodians or relatives. The FIT model project at the UKT is, together with all other FIT projects at hospitals so far, based on a global treatment budget (i.e. fixed annual budget for all treated patients including inpatient care, day care and outpatient care [16]), but supplemented by additional revenue compensation. The focus of this model project is, however, based on the model specific element TIBAS, which is remunerated via per diem rates.

The study design presented here describes the evaluation of the FIT model project at the KJP of the UKT (EVA_TIBAS). The aim of the evaluation is to examine the achievement of the objectives of the FIT model project and to assess the transferability of the care approach into standard care. The primary objectives of the model project are
to shorten the duration of inpatient stays while intensifying outpatient forms of treatment,to reduce the cumulative psychiatric treatment duration and the emergency admission rate,to reduce the symptom burden, to accelerate the return to psychosocial living conditions andto increase the quality of life.

The primary outcome measures for this evaluation are the change in inpatient psychiatric treatment and in quality of life. Stabilization of the family’s overall care situation will be used to sustain these improvements. Using qualitative research methods, the experiences with and the subjective benefit of the social service of the AOK Baden-Württemberg as well as the cooperation of this social service with the UKT will be examined in more detail. In addition, the costs of the FIT model care should not exceed those of the standard care or, at a maximum of the same costs, better results should be achieved with regard to the above-mentioned patient-related goals.

The EVA_TIBAS evaluation study will examine the FIT model project’s effectiveness in terms of treatment and patient-related outcomes, direct medical and indirect costs, and cost-effectiveness of the model compared to standard care.

## Methods/design

### Overall design

#### General

EVA_TIBAS is a controlled cohort study using a mix of quantitative and qualitative methods. The evaluation consists of three modules. In Module A, anonymized SHI claims data will be used to compare patients treated in the model hospital, i.e. KJP at the UKT, where the above described FIT model project is implemented and under evaluation (intervention group (IG)), with patients treated in control hospitals, i.e. structurally comparable hospitals from the federal state of Baden Württemberg (control group (CG)). In Module B, patient-reported outcomes will be quantitatively assessed using validated questionnaires in the model and two control hospitals. In Module C, semi-structured interviews and a focus group discussion will examine the additional offer of the social service of the AOK Baden-Württemberg in the IG (Table 1).

**Table.1 Tab1:** Overview study design modules

Module	design	Intervention Group	Control group	time frame	data	outcomes
A	Cohort study, retrolective	Patients treated between Jan 2018 and Dec 2021 in the KJP of the UKT and insured with the SHI fund AOK Baden-Württemberg; *n* = ca. 600	Matched patients from up to 10 control hospitals treated between Jan 2018 and Dec 2021	Two years before and one to four years after reference date	Anonymized data from SHI fund AOK Baden-Württemberg	Duration of inpatient and day care psychiatric treatment, inpatient and day care psychiatric length of stay, outpatient psychiatric treatment in hospital, inpatient hospital readmission, emergency admission rate, direct medical care costs, and cost-effectiveness
B	Cohort study, prospective	Patients of the KJP of the UKT, insured with the SHI funds AOK Baden-Württemberg or SVLFG and treated within 18-month recruitment phase starting autumn 2021 (baseline); *n* = ca. 300	Patients from two structurally comparable hospitals (control hospitals) treated within 18-month recruitment phase starting autumn 2021	Baseline starting autumn 2021 and follow-up with 24 months after recruitment	patient-reported quantitative data	Health-related quality of life, symptom burden, return to psychosocial relationships, treatment satisfaction, societal costs, and cost-effectiveness
C	Cross-sectional					
C1	Semi-structured Interviews	Families of patients being treated in the KJP of the UKT, insured with the SHI fund AOK Baden-Württemberg and treated within 18-month recruitment phase starting autumn 2021 and with social service recommendation; *n* = ca. 30	NA	Between autumn 2021 and spring 2023	Personal telephone interviews	Offer and effects of social service, benefit from social service
C2	Focus group	UKT & social service personnel	NA	Spring 2022	Focus group discussion	Cooperation between UKT and social service employees

*KJP* Department of child and adolescent psychiatry, *UKT* University Hospital Tübingen, *SHI* Statutory health insurance, *reference date* First treatment in either intervention or control hospitals between 01 January 2018 and 31 December 2021, *n* Anticipated number of study participants in each module; *NA* Not applicable

In order to ensure that potential outcome-related differences between IG and CG can be attributed solely to the intervention, both groups have to be as similar as possible to each other regarding all other aspects. Group comparability will be established in a two-step procedure. First, structurally comparable control hospitals were defined (see “selection of control hospitals” below). Second, from those identified control hospitals appropriate, comparable patients must be selected (see module descriptions). Further explanations of each module are given below. Figure 1 visualizes the study data flow in each of the modules.

**Fig. 1 Fig1:**
[figure not shown]
Study data flow chart

The study team is supported by an advisory board with representatives from the German Society for Child and Adolescent Psychiatry, Psychosomatics and Psychotherapy (DGKJP) and the Federal Association of Relatives of Mentally Ill People e.V. (BApK), who give advice regarding study initiation, implementation and result interpretation.

### Outcomes and hypotheses

Each module targets different research questions and underlying hypotheses (Fig. 2).

**Fig. 2 Fig2:**
[figure not shown]
Outcomes and Hypotheses

#### Primary outcome measures

Duration of inpatient psychiatric treatment (Module A), i.e. the average cumulative inpatient psychiatric treatment duration (based on all included patients)Health-related quality of life (Module B), i.e. self-rated quality of life

#### Secondary outcome measures

Duration of day care psychiatric treatment (Module A), i.e. the average cumulative day care psychiatric treatment duration (based on all included patients)Inpatient psychiatric length of stay (Module A) (based only on cases with inpatient psychiatric treatment)Day care psychiatric length of stay (Module A) (based only on cases with day care psychiatric treatment)Outpatient psychiatric treatment in the hospital (Module A), i.e. the intensity of outpatient psychiatric treatment in the hospital (PIA or TIBAS)Inpatient hospital readmission (Module A), i.e. percentage of patients with at least one second inpatient hospital stay within 12 months after discharge from first inpatient hospital stayEmergency admission rate (Module A), i.e. the percentage of patients with any psychiatric diagnosis (ICD-10: Fx) and emergency admission relative to all inpatient admissions with any psychiatric diagnosis within the respective reference hospital (either IG or CG)Direct medical care costs (Module A), i.e. the direct medical care costs of the psychiatric services from an SHI perspectiveCost-effectiveness (direct medical costs) (Module A), i.e. comparison between duration of inpatient psychiatric treatment and direct medical care costs (SHI perspective)Symptom burden (Module B), i.e. measure of emotional symptoms, conduct problems, hyperactivity/inattention, peer relationship problems, and pro-social behaviorReturn to psychosocial relationships (Module B), i.e. measure of social integration (friends, school, sports activity, hobbies, social inclusion, day structure)Treatment satisfaction (Module B), i.e. self-perceived satisfaction with treatmentSocietal costs (Module B), i.e. costs from a societal perspective including additional costs not covered by the SHI funds, patients’ and relatives’ care, and travel expensesCost-effectiveness (societal costs) (Module B), i.e. comparison between health related quality of life and societal costs (societal perspective)Offer and effects of social service (Module C), i.e. how families (with and without utilization of the social service) assess the social service offered by the AOK Baden-Württemberg and which additional effects do they experience using this serviceBenefit social service (Module C), i.e. to what extent do the users see a benefit in the advisory support provided by the social serviceCooperation between UKT and social service employees (Module C) i.e. how the professional representatives of the UKT assess the cooperation with the social service of the AOK Baden-Württemberg and which strengths and optimization potentials are mentioned

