### Module A

#### Design

Module A describes the resource utilization in the model hospital including the shift from inpatient to outpatient treatment in the hospital, clinical outcomes and direct medical costs. Anonymous claims data from the SHI fund AOK Baden-Württemberg will be analyzed. Results will be separately analyzed between patients who have not been treated in the reference hospital, either model or control hospital, during the 2 years before study entry (hospital-new patients) and those who were treated at least once in the hospital in the 2 years before study entry (hospital-known patients).

All patients treated in the KJP at the UKT between January 2018 and December 2021 on an inpatient or outpatient basis, insured with the SHI fund AOK Baden-Württemberg and with follow-up data of at least 12 months after reference treatment will be included in the analysis for the IG. Due to the low number of those insured with the SHI fund SVLFG, this SHI will not be included in this analysis. The first 3 months after model project start (October – December 2017) will not be considered in this analysis due to initially incomplete implementation of model structures and benefit from consideration of complete calendar years. Patients selected via PIA treatment must be younger than 18 years of age at the time of the reference treatment.

Patients for the CG will be matched with patients from the above-described selected control hospitals. For each patient in the IG, one control patient will be matched from the patient pool of the selected control hospitals. For this purpose, two linked two-stage or mixed propensity score matches will be performed. The final decision about the consideration of patients for the analysis will be made using initial available data (power simulation).

The reference case refers to the initial treatment of the patient in either IG or CG after study onset, i.e. inclusion into the study in Module A. The reference date (Module A) refers to the date of the reference case. Outcomes in Module A will be compared to patients’ results 1 year prior to the reference case (pre-period) to better estimate the effect of FIT treatment.

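### The emergency admission rate divides patients by inpatient admissions, a denominator FIT may itself change, so it can rise or fall with no change in emergencies

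*Protocol article*

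**What the plan says.** Secondary outcome measures sets the numerator as "the percentage of patients with any psychiatric diagnosis (ICD-10: Fx) and emergency admission" and fixes the denominator with the words "emergency admission relative to all inpatient admissions with any psychiatric diagnosis within the respective reference hospital", where the reference hospital is the model or a control hospital. Background lists among the primary objectives of the model project "to reduce the cumulative psychiatric treatment duration and the emergency admission rate", so a lower value counts as success.

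Three statements bear on how FIT could affect inpatient admissions:

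- Background, objectives: "to shorten the duration of inpatient stays while intensifying outpatient forms of treatment".
- Module A, Design, on what the module describes: "including the shift from inpatient to outpatient treatment in the hospital".
- Background, on alternatives to inpatient care under the current financing: "often not financially covered leading to more-than-necessary inpatient treatment".

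The Module A cohort takes in patients treated "on an inpatient or outpatient basis, insured with the SHI fund AOK Baden-Württemberg", so it can include patients who are never admitted. The Module A primary outcome is averaged over every included patient. Module A, Analysis applies a difference-in-difference comparison to all outcomes of the module except readmission.

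**The concern.** There are two faults in one definition.

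First, the units do not match. As worded, a patient with two emergency admissions counts once above the line and twice below it, so the result is not a true percentage. It also depends on how often patients are readmitted.

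Second, the denominator is counted after treatment starts and depends on admission practice, which the model project may alter. A change in planned admissions moves the rate even if the number of emergencies stays the same. Success in moving care out of the ward could then read as failure on the emergency objective. Conversely, extra planned readmissions could read as success. The result is meant to inform policy makers on a named objective, so the rate needs to respond to emergencies and not to the volume of other admissions.

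**Working it through.** The article gives no target value, expected effect or power for this outcome, so there is no figure of the plan to reproduce. The check is algebra with illustrative inputs.

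**Inputs**

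- p, baseline share of admissions that are emergencies: 38% (2013) and 29% (2011), the German background figures in Background. They are not planning values for these hospitals. Treating them as shares of admissions is an assumption.
- e, relative fall in emergency admissions under FIT: not given, assumed.
- x, relative fall in planned admissions under FIT: not given, assumed from a 50% fall to a 20% rise (x = −0.2).
- To isolate the denominator effect, each emergency patient is taken to have one emergency admission.

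**Formula**

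rate = p(1 − e) / [p(1 − e) + (1 − p)(1 − x)]

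The rate exceeds p when (1 − e) > p(1 − e) + (1 − p)(1 − x). This reduces to (1 − e) > (1 − x), that is, x > e. So the rate rises whenever planned admissions fall proportionately more than emergencies, and falls in the opposite case.

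**Emergencies unchanged (e = 0), per 100 baseline admissions**

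| Planned admissions | Baseline 38% | Baseline 29% |
|---|---|---|
| unchanged (shorter stays only) | 38/100 = 38.0% | 29/100 = 29.0% |
| −10% | 38/93.8 = 40.5% | 29/92.9 = 31.2% |
| −30% | 38/81.4 = 46.7% | 29/78.7 = 36.9% |
| −50% | 38/69.0 = 55.1% | 29/64.5 = 45.0% |
| +20% | 38/112.4 = 33.8% | 29/114.2 = 25.4% |

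**Emergencies falling as well**

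- e = 10%, x = 20%, from 38%: 34.2/(34.2 + 49.6) = 40.8%.
- e = 10%, x = 20%, from 29%: 26.1/(26.1 + 56.8) = 31.5%.
- e = 15%, x = 30%, from 38%: 32.3/(32.3 + 43.4) = 42.7%.

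In each of these cases a real reduction in emergencies shows as an increase.

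**Difference-in-difference**

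Suppose the control group stays at 38% and planned admissions fall 30% in the intervention group with emergencies unchanged. The estimate is (46.7 − 38.0) − (38.0 − 38.0) = +8.7 percentage points. The control group removes changes common to both groups. A change in admission practice caused by FIT is not common to both, so it stays in the estimate.

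**Units**

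A patient whose only two admissions are both emergencies contributes 1/2 = 50%, although every admission was an emergency. More repeat emergencies per patient lower the rate.

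**Alternative denominator**

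Counted per included patient or patient-year, the measure does not move when emergencies are unchanged, whatever x is. It falls 10% when emergencies fall 10%.

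**The case against.** The strongest objection concerns the premise. A reader might infer that FIT is designed to cut admissions, so that the denominator must shrink in the intervention group alone and the rate is biased against FIT. The article does not support that. Its explicit objective is shorter stays, and Background describes the intensive outpatient treatment as enabling earlier discharge. Both concern days, whereas the denominator counts admissions. Fewer admissions is a plausible inference from the shift of setting and the remark on excess inpatient treatment, but it is not a stated aim. If only stays shorten, the rate does not move through this route. If earlier discharge brings planned readmissions, the distortion favours FIT. This objection stands, and it limits the point to a rate that can err in either direction.

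The assumed changes in planned admissions have no source in the article, and with a 10% fall the shift is only 2.5 points from 38%. That also stands, so the figures show sensitivity and do not forecast a bias.

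It can further be said that the share of admissions that are unplanned is a legitimate quantity, that the article is condensed, and that the figure on outcomes and hypotheses is not shown. The share is indeed worth reporting. But the article states numerator and denominator explicitly, and as stated they have different units and are exposed to admission volume. For an evaluation of FIT, an all-patient denominator answers the emergency question more directly. Other planned outcomes, such as cumulative inpatient duration and outpatient intensity, give context but do not correct this rate.

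**Conclusion.** The point holds in a limited form. As defined, the emergency admission rate mixes patients with admissions and can change without any change in emergencies. It rises if planned admissions fall proportionately faster than emergencies, falls if planned admissions increase, and is unaffected by this mechanism if admission numbers stay the same. That direction rule is exact under the simplification of one emergency admission per patient. The size is not known from the article. From a 38% baseline with emergencies constant, the assumed scenarios run from 33.8% to 55.1%; from 29%, they run from 25.4% to 45.0%. The difference-in-difference comparison does not protect against a FIT-specific change in admissions.

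The consequence is confined to one secondary outcome, though one tied to a listed objective of the model project. The primary outcomes and their analyses are unaffected.

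**What to change.** Redefine the outcome on all included patients, as Primary outcome measures does for inpatient treatment duration. Use either emergency psychiatric admissions per patient-year or the share of included patients with at least one such admission. Compute it for each patient-specific year, with the same rule in both groups. Keep the share of psychiatric admissions that are emergencies as a descriptive figure, with admissions in both numerator and denominator, and report the numbers of emergency and planned admissions beside it so that readers can see which part moved.

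The cost is the rewording of one outcome definition; the claims data already planned for Module A suffice. The drawback is less direct comparability with admission-based rates, which the descriptive share partly offsets.

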Effects and costs will be analyzed from a SHI perspective. Primary (confirmatory) analyses will be performed according to the intention-to-treat approach firmly assigning patients to the hospital that initially filed their reference case. For the cost-effectiveness analysis, primary outcome parameters and costs will be compared between model and control hospitals using the incremental cost-effectiveness ratio as costs per one-day-of-hospital-stay avoided. A significance level of *p* ≤ 0.05 will be set for all analyses.

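### Module A's payer cost, as defined, leaves out the fund's own social service, which is part of FIT, and claims may not equal what the fund pays under its budget contract

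*Protocol article*

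**What the plan says.** The Secondary outcome measures section defines the Module A cost outcome as "the direct medical care costs of the psychiatric services from an SHI" perspective. Module A, Design, gives the source: "Anonymous claims data from the SHI fund AOK Baden-Württemberg will be analyzed". Module A, Analysis, adds "Effects and costs will be analyzed from a SHI perspective" and uses the cost in an incremental cost-effectiveness ratio per hospital day avoided. The goal that these results bear on is in the Background: "the costs of the FIT model care should not exceed those of the standard care", or better results at no more than equal cost.

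The Background also describes what FIT consists of and how it is paid:

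- The social service of the contracting fund supports patients and especially families through psychosocial counselling and networking with other providers. Overall design calls it an additional offer in the intervention group.
- The model hospital has a "fixed annual budget for all treated patients including inpatient care, day care and outpatient care", "supplemented by additional revenue compensation". TIBAS is paid by per diem rates.

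Module C evaluates the social service qualitatively only. The section on strengths and limitations presents the claims data as supporting a comprehensive assessment of costs and lists no limitation tied to the funding model.

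**The concern.** A payer-perspective comparison should count what the payer spends on each form of care. Here a component of the intervention lies outside the cost definition, while its effect lies inside the outcome definition. The Background expects stabilisation of the family's care situation to sustain the improvements, so the service can contribute to fewer inpatient days. The ratio per day avoided could then credit FIT with days that the social service helped to avoid, without charging for that service.

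The second question is whether patient-level claims represent the fund's spending at a hospital paid by a fixed budget with compensation. If they do not, the claims difference and the payer difference are two different quantities.

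Both matter because the Conclusions section says the results are to inform policy makers on adoption into standard care.

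**Working it through.** The article states no cost, standard deviation, cost margin, budget or compensation amount, so there is no cost figure of the plan to reproduce. The check compares the definitions and then uses the article's own counts.

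**1. Is the social service inside the Module A cost?** The outcome is limited to direct medical costs of psychiatric services taken from claims. The service is psychosocial counselling and networking by the fund's own staff. It is not a psychiatric service in that sense, and nothing in Module A adds it. It is therefore excluded by the wording of the outcome, not merely left unmentioned.

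**2. Does the difference-in-difference approach remove the omission?** Write the estimated cost effect as (IG after − IG before) − (CG after − CG before). The service is described as an additional offer in the intervention group under the model, so its cost falls essentially in the first term only. A cost that is absent from the data and specific to one term is not differenced out.

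**3. How many users per intervention patient?**

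- Module C, Analysis: 25% of 150 recommended families = 37.5, given there as 38, in 18 months.
- Module A, Analysis: 120 intervention patients within one year, so 1.5 × 120 = 180 in 18 months. Users per patient: u = 38/180 = 0.21.
- Alternative denominator from the same section: 300 intervention patients in the final dataset covering four years. Users: 38/1.5 = 25.3 per year, times 4 = 101. Then u = 101/300 = 0.34.

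Both values are rough. The user count belongs to a recruitment phase starting in autumn 2021, whereas Module A patients enter from 2018 to 2021. The 25% are also families expected to contact the service, with no statement of how intensively they use it.

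**4. What does this do to the cost results?** Let c be the unknown cost per user family, D the claims-based saving per intervention patient and E the days avoided per patient.

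- Cost difference with the service included: −D + u·c.
- Cost-effectiveness ratio: shifted by u·c/E.
- The service alone reverses a saving only if c exceeds D/u. That is 180/38 = 4.7 times D with the first denominator, or 300/101 = 3.0 times D with the second.

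The direction is known, because the omission understates FIT cost. The size depends on c, which the article does not give.

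**5. Claims against budget.** Let S be the sum of claims at the model hospital and P what the fund finally pays. Under a fixed budget with compensation, P − S need not be zero. The article gives none of the following: the budget, the compensation, whether any settlement appears in the claims, how TIBAS per diems relate to the budget, or how control hospitals are settled. Neither the size nor the sign of P − S, nor of its difference between groups, can be derived.

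**The case against.** The strongest objection is that an article gives only a short outcome label and leaves the valuation of costs to the full plan. An SHI perspective could be read as already meaning everything the fund pays. This stands in part for the budget question, where the article is silent on settlement. It does not remove the social-service point, because the stated definition is restricted to psychiatric services and further unit-cost detail would not widen it.

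Two stronger readings are tempting, and the documents support neither.

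- A reader might infer that the social service is costed nowhere in the study. Module B collects costs with a custodian questionnaire adapted partly from an instrument on medical and non-medical services (Table 2), which may record its use. The societal cost definition also adds items not covered by the funds without restricting itself to them. The gap is established for Module A only.
- A reader might infer that claims savings are paid back through the budget, so that FIT is bound to look too cheap. That would need the size and sign of the compensation, which are not given. Control hospitals may have similar settlements, and TIBAS per diems raise claims as inpatient claims fall. Any assumed percentage saving would be an illustration, not evidence of magnitude.

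It is also fair to say that claims-based patient cost is a defensible main measure when the question is transfer to standard care. Spreading hospital-level budget totals over patients or days is debatable. This is a reason to keep the budget correction out of the main analysis.

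**Conclusion.** The Module A cost definition omits a component of FIT, and this understates FIT cost to the payer in both the cost comparison and the ratio per day avoided. The conclusion rests on two assumptions: that the fund bears the cost of its own social service, which is inferred, and that control families do not receive the same service under standard care, which follows from its description as an additional offer. The amount is about 0.21 to 0.34 times the cost per user family, per intervention patient. Unless that unit cost is several times the claims-based saving, the omission does not reverse the result by itself; near break-even it could.

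The budget and compensation issue is an open question about what the claims represent. It is not a demonstrated bias, and its size and direction are unknown. Overall this is a cheap improvement to the plan. It does not show that a finding of no higher cost would be wrong.

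**What to change.** In Secondary outcome measures and Module A, Analysis:

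- Extend the intervention group's cost by the fund's annual social-service cost for model-hospital families, averaged per intervention patient. Use this figure in the main cost comparison and in the cost-effectiveness ratio.
- Add a sensitivity analysis that includes revenue compensation and budget settlement for the model hospital, and for control hospitals where such payments exist.
- State in advance that, if this sensitivity analysis changes the answer, the conclusion that FIT costs no more will be limited to a claims-based statement.

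The cost is a few annual totals from the fund, which is both contract partner and data provider. No patient-level linkage is needed, so the anonymity of the claims data is unaffected. The downside is that an average is assigned evenly to all patients: it shifts the estimate but carries no information on variation between patients. FIT may also look slightly less favourable.
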